## Abstract

**Introduction::**

Chronic pain, fatigue and insomnia are classic symptoms of fibromyalgia (FM) and chronic fatigue syndrome (CFS) and seriously affect quality of life. Nutrition and chronobiology are often overlooked in multicomponent approach despite their potential. This study aims to evaluate the effectiveness of a multidisciplinary group intervention based on nutrition, chronobiology, and physical exercise in the improvement of lifestyle and quality of life in FM and CFS.

**Methods::**

Mixed-methods study based on a randomized clinical trial and qualitative analysis with a descriptive phenomenological approach. The study will be conducted in primary care in Catalonia. The control group will follow the usual clinical practice and the intervention group the usual practice plus the studied intervention (12 hours over 4 days). The intervention based on nutrition, chronobiology and physical exercise will be designed considering participants’ opinions as collected in 4 focus groups. To evaluate effectiveness, EuroQol-5D, multidimensional fatigue inventory, VAS pain, Pittsburgh Sleep Quality Index, erMEDAS-17, biological rhythms interview of assessment in neuropsychiatry, REGICOR-Short, FIQR and Hospital Anxiety and Depression Scale questionnaires will be collected at baseline, and at 1, 3, 6, and 12 months post-intervention. Food intake, body composition, resistance and, strength will also be evaluated. The effect size will be calculated using Cohen d and logistic regression models will be used to quantify the impact of the intervention by adjusting for different variables.

**Discussion::**

It expected that the intervention will improve the patients’ quality of life, fatigue, pain and insomnia, as well as food and physical exercise habits, providing effectiveness evidence of a new therapy in addressing these syndromes in Primary Heath Care. Improvements in the quality of life will have a positive socioeconomic impact by reducing health expenditure on recurrent medical consultation, medication, complementary medical tests, etc and favor the maintenance of an active working life and productivity.

## 1. Introduction

Fibromyalgia (FM) and chronic fatigue syndrome (CFS) are considered central sensitization syndromes and involve neurological, metabolic and immunological circuits. Widespread pain, fatigue, and insomnia are the main symptoms of these conditions and seriously affect quality of life, especially in women.^[1]^

The etiopathogenesis of FM remains unclear and controversial,^[2]^ and there are currently no biomarkers or specific medical tests available for it.^[3]^ The prevalence of FM is estimated to be between 0.02% and 6.6% globally^[4]^ and 2.45% in the Spanish population.^[5,6]^ The annual cost per patient in industrialized countries is estimated to be €7256 to €7900, and the indirect costs (loss of productivity) are considered greater than direct ones (medical visits, prescriptions, etc).^[6]^ FM thus represents a high cost for society, estimated at €12.9 million in Spain in 2017.^[7]^

CFS, which often overlaps with FM,^[8,9]^ affects all ages and socioeconomic groups, although it is most common in the 30 to 50 age group. The estimated prevalence in the United States is 0.42%, of which 70% are women.^[10]^ This represents an annual cost of $17 to $24 million.^[11]^ There are no updated data on the incidence of CFS in Europe, but it is estimated to currently affect around 2 million people.^[12]^

The pharmacological treatments currently used in FM are only partially effective, and patients do not improve as expected. The disease becomes chronic and presents in the form of flare-ups, resulting in no positive impact either for patients or the healthcare system. Therefore, recent research on FM treatment focuses on evaluating non-pharmacological multicomponent interventions that involve various disciplines (physical therapy, psychology, and health education).^[6]^ The results of this type of multidisciplinary treatment are positive and have been shown to decrease pain and improve quality of life.^[13,14]^ These interventions were mainly based on cognitive-behavioral therapy, physical activity, and health education, often with very limited or no emphasis on nutrition or chronobiology.

However, there is increasing evidence of the impact of nutrition and chronobiology on different aspects of health and disease, including the impact on central sensitization syndromes such as FM and CFS.^[15–18]^ It is therefore worth including these approaches in the design of non-pharmacological multicomponent interventions. FM has been associated with oxidative stress, mitochondrial dysfunction, and autonomic dysregulation, among other factors. Moreover, several studies associate eating habits, low levels of certain micronutrients (iron, vitamin D, vitamin B12, vitamin B9, vitamin C, vitamin E, essential and branched amino acids, etc), and abnormal body composition to changes in metabolism and energy regulation, and, thus, in the development and impact of FM.^[19–22]^ Other studies show that nutritional interventions aimed at preventing or rebalancing deficiencies of certain micronutrients can improve symptoms, although specific studies and recommendations are lacking.^[1,23,24]^ The relevance of some nutritional deficiencies and low levels of certain nutrients (vitamin C, vitamin B complex, sodium, magnesium, zinc, folic acid, L-carnitine, L-tryptophan, essential fatty acids, coenzyme Q10, etc) has also been highlighted as potentially playing a role in the severity of symptoms associated with CFS.^[25]^

While still scarcely addressed in primary care studies, chronobiology is gaining importance due to the impact it can have in the prevention, triggering and progression of various diseases. Circadian rhythms are particularly relevant in metabolism, hormonal regulation, and cellular repair mechanisms. CFS has recently been associated with various chronobiologic indicators, such as sleep quality, which seem to play a significant role in the development and progression of the syndrome.^[17,18]^ Recent studies also show the impact and relevance of chronobiology in FM.^[26]^ Therefore, chronobiology should be included in depth as an innovative factor in multidisciplinary approaches aimed at preventing and improving chronic diseases. Furthermore, several studies demonstrate the positive impact that approaches involving physical exercise can have on FM and CFS.^[13,17,27]^ Moreover, there are significant interrelationships between nutrition, chronobiology, and physical exercise. The meal times and morning physical exercise contribute to the regulation of circadian clock and, therefore, improve insomnia and fatigue.^[28]^ Exposure to sunlight, especially in the morning, also contributes to the regulation of circadian clock and reduce insomnia.^[29]^ On the other hand, a balanced diet and adequate exercise help to improve body composition and increase muscle mass, which in turn improve metabolism and thus facilitate a more active life with increased exercise and less fatigue.

Although FM and CFS have been associated with certain patterns of food intake and alterations to biological rhythms, most of the studies reviewed to date do not investigate whether these factors play a role in the development of these syndromes or are the result of having them. In any case, an intervention aimed at improving these 2 aspects could have a positive impact on the quality of life of these patients.

This study aims to evaluate the effectiveness of a new short and intensive multicomponent group therapy based on nutritional, chronobiological and physical exercise education. The program will be designed and optimized taking into account the opinions of participants diagnosed with FM, with or without CFS. We designed a complex intervention based on the Medical Research Council methodology, including quantitative and qualitative phases^[30–32]^ so that we can better adapt it to people needs and the setting in which it is implemented. The objective is to encourage patients to adhere to healthy lifestyle habits (nutrition, chronobiology, and physical exercise) to improve fatigue, pain and insomnia and, therefore, quality of life.

## 2. Methods

### 2.1. Study design and intervention description

Study design: Mixed-methods study that includes a nonblinded, pragmatic randomized clinical trial with parallel groups and a qualitative study with 4 focus groups (two pre-intervention and 2 post-intervention) with a descriptive phenomenological approach. The control group will follow the usual clinical practice, consisting of an individual visit with the FM specialist, who will conduct a standardized medical history and inform the patient of the disease using a custom designed leaflet.^[33]^ The intervention group will follow the usual practice plus the intervention under study (Fig. 1).

**Figure 1. F1:**
[figure not shown]
Flow diagram of the study.

Description of the intervention: The intervention to be evaluated is multicomponent and based on actively educating people diagnosed with FM, with or without CFS, on nutrition, chronobiology and physical exercise. It consists of 4 group sessions conducted over 2 consecutive weeks, 6 hours per week on 2 days, 3 hours per day (for a total of 12 hours) (Fig. 2). Data will be collected for both groups and related to quality of life, symptoms, fatigue, pain, nutrition, nighttime rest, body composition parameters, strength, and endurance, before intervention and during follow-up at 1, 3, and 6 months after intervention. The data analysis results will be used to evaluate the effectiveness of the intervention, and the focus group results will be used to optimize the intervention.

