### 3.2. Data collection

Sample size and sampling procedure: The sample size was calculated by GRAMNO V7.12. sample size calculation program and is based on the variations we expect to observe in the EuroQol-5D questionnaire on health-related quality of life.^[35]^ Accepting an alpha risk of 0.05 and a beta risk of <0.05 in a 2-tailed test, a minimum of 43 subjects are needed in each group to detect a minimum difference of 1.6 between 2 groups, with a standard deviation of 1.8. The loss to follow-up rate was estimated at 20%.

Patients diagnosed with FM (ICD-10 code M79.7) with or without CFS (Myalgic encephalomyelitis, code G93.3) treated at Terres de l’Ebre ICS Primary Care (Catalonia) and who meet inclusion criteria will be contacted by phone and invited to participate in the study. Patients will be asked to come to the health center for the first visit, where the study will be explained, and informed consent signatures will be collected. A randomization list will be generated following Efron procedure^[46]^ and using the statistics program SPSS. At this visit, the patient will be informed of which group they will participate in (control or intervention) and the schedule of sessions (or visits). Additionally, the baseline data will be collected from self-administered questionnaires (EuroQol-5D, multidimensional fatigue inventory, VAS pain, Pittsburgh Sleep Quality Index, erMEDAS-17, biological rhythms interview of assessment in neuropsychiatry, REGICOR-Short, FIQR, Hospital Anxiety and Depression Scale) using Microsoft Forms or paper if participants have difficulty using technology. These data will be collected again at 1, 3, 6, and 12 months post-intervention (Table 1). Data will also be collected in person at baseline and at 3 and 6 months post-intervention to evaluate the food intake, body composition, strength and endurance of study participants. These data will be collected from both the intervention and control groups and will be entered into an Excel database for use in the various analyses.

**Table 1 T1:** Data collection planning.

Data collection	Baseline	1m post	3m post	6m post	12m post
To assess quality of life and symptoms, chronobiology and healthy habits (ONLINE):					
*EuroQol-5D: quality of life*	X	X	X	X	X
*MFI (20-items): fatigue*	X	X	X	X	X
*VAS pain: visual analogue pain intensity scale*	X	X	X	X	X
*PSQI (19 items): sleep quality*	X	X	X	X	X
*BRIAN: biological rhythm*	X	X	X	X	X

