### 3.3. Statistical analysis

To measure the effect of the intervention within each group, and in the same group before and after intervention, the effect size will be calculated using Cohen d,^[47]^ which classifies effect size as small (0.2–0.5), moderate (0.5–0.8), or large (>0.8). Lastly, logistic regression models will be used to measure the impact of the intervention on improved quality of life by adjusting for any variables that may be considered confounding variables from a clinical point of view.

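### The intervention is taught in group courses but the 43 per arm assume independent patients, so the stated power is overstated for any positive within-course correlation

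*Protocol article*

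**What the plan says.** Section 2.1 of the protocol article describes the studied therapy as teaching delivered to groups: "It consists of 4 group sessions conducted over 2 consecutive weeks", with 12 hours of contact in total. The same section gives controls an individual visit with a specialist and a leaflet. Under section 3.2, each patient is allocated from a randomisation list, so the unit of randomisation is the patient.

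Section 3.2 sizes the trial as an ordinary two-group comparison of EuroQol-5D means: "Accepting an alpha risk of 0.05 and a beta risk of <0.05 in a 2-tailed test". The requirement it derives is "a minimum of 43 subjects are needed in each group to detect a minimum difference of 1.6 between 2 groups". The SD is taken as 1.8 and the expected loss as 20%. It gives no course size, number of courses, ICC or design effect.

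Section 3.3 names Cohen d and a regression: "logistic regression models will be used to measure the impact of the intervention on improved quality of life". That regression includes clinically chosen confounders. Course is not mentioned there, among the independent variables in section 3.1, or in Table 1.

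**The concern.** Patients taught together share peers, dates and 12 hours of discussion. Their later self-reported quality of life, in a nonblinded trial, can plausibly be more alike than that of patients from different courses. Controls have no such shared exposure. If the ICC within courses is positive, the intervention mean is less precise than its number of patients suggests.

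Two things follow. The power claimed in section 3.2 is too high, and any standard error that ignores course is too small, so that a nominal 5% test rejects too often. This matters because the Discussion expects a confirmed benefit to lead to updated primary care guidelines.

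**Working it through.** **Inputs from section 3.2.** Difference 1.6, SD 1.8, two-sided alpha 0.05, power 0.95 (beta <0.05), loss 20%, 43 per group.

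**Inputs assumed, because the protocol gives none.** Course size m from 8 to 15 and ICC from 0.01 to 0.10. Total SD is held at 1.8.

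**Step 1. Reproduce the 43.** By normal approximation, n = 2 × 1.8² × (1.960 + 1.645)² / 1.6² = 32.9, so 33 per arm. A two-sample t-test needs 34 (power 94.5% with 33, 95.1% with 34). Then 34 / 0.8 = 42.5, rounded up to 43. Power of 80% or 90% with 20% loss would give 25 or 34 per arm by normal approximation, so 43 corresponds to 95% power with loss included. In reverse, 43 × 0.8 = 34.4, or about 34 completers. The loss allowance uses up the whole excess over 34.

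**Step 2. Add clustering in one arm.**
- Design effect in the intervention arm: DE = 1 + (m − 1) × ICC.
- Standard error of the difference: 1.8 × √((1 + DE) / 34).
- Ratio to the independent-patients standard error: R = √((1 + DE) / 2).
- Power: Φ(1.6 / SE − 1.96).
- True level of a test of means that ignores course: 2 × (1 − Φ(1.96 / R)).

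Example, m = 10 and ICC 0.05: DE = 1 + 9 × 0.05 = 1.45. SE = 1.8 × √(2.45 / 34) = 0.483. Power = Φ(3.311 − 1.96) = 91.2%. R = √1.225 = 1.107 and the level is 7.7%.

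**Step 3. Allow for few courses.** With 34 completers there are k = 34 / m courses, about 2 to 4. If the variance of the intervention mean is estimated between courses, the Satterthwaite degrees of freedom are (1 + DE)² / (1/33 + DE² / (k − 1)). Power then comes from the noncentral t distribution with noncentrality 1.6 / SE. For m = 10 and ICC 0.05, k = 3.4, df = 2.45² / (0.030 + 1.45² / 2.4) = 6.6, and power is 80%.

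| m | ICC | DE | R | Power, normal | True level | Power, Satterthwaite |
|---|---|---|---|---|---|---|
| any | 0 | 1.00 | 1.00 | 95.6% | 5.0% | see below |
| 8 | 0.01 | 1.07 | 1.02 | 95.0% | 5.4% | 91% |
| 15 | 0.01 | 1.14 | 1.03 | 94.3% | 5.8% | 78% |
| 8 | 0.05 | 1.35 | 1.08 | 92.2% | 7.1% | 86% |
| 10 | 0.05 | 1.45 | 1.11 | 91.2% | 7.7% | 80% |
| 15 | 0.05 | 1.70 | 1.16 | 88.4% | 9.2% | 59% |
| 10 | 0.10 | 1.90 | 1.20 | 86.1% | 10.4% | 70% |
| 15 | 0.10 | 2.40 | 1.30 | 80.3% | 13.3% | 43% |

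The last column includes a price paid for having few courses, even without correlation. At ICC 0 it is 92% for m = 8, 90% for m = 10 and 83% for m = 15.

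**The case against.** A reader might infer that the stated power fails on the protocol's own inputs. It does not. Those inputs give 95.1% power with 34 completers per arm, and the shortfall appears only once an ICC and a course size are assumed. At ICC 0.01 the normal-approximation loss is about one point, which is negligible. If 43 were read as completers, power at m = 10 and ICC 0.05 would stay near 96%. However, the figure reproduces only with the 20% loss included, so that reading is hard to sustain.

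The analysis part is weaker than the sample-size part. Section 3.3 is a short summary in an article, it does not exclude a course term, and an SAP could supply one. The sample-size statement is different: a course term added later would not restore the claimed 95%.

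The error rates of 5.4-13.3% belong to a comparison of two means. Nothing was computed for the logistic model, and Cohen d is presented as an effect-size classification and not as a test. The figures therefore show scale and are not the error rate of the stated analysis.

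Finally, the protocol does not say who teaches. If one team teaches every course, educators add no correlation between patients of the same course beyond that shared by all courses. Shared peers and dates remain. All these points limit the size of the claim, and none changes its direction.

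**Conclusion.** The point stands in conditional form. It is certain that the design is partially nested and that 43 per group contains a loss allowance but none for clustering. For any positive ICC the stated power is overstated, and standard errors that ignore course are too small.

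The magnitude cannot be fixed from the protocol. On the assumptions above it runs from negligible (ICC 0.01, normal approximation) to material (power 80% and level 13% at m = 15, ICC 0.10). An analysis that respects the small number of courses has less power again, about 80% at m = 10, ICC 0.05 and about 43% at m = 15, ICC 0.10. The documents do not support saying that the trial is underpowered on its own figures, or that the final analysis will certainly ignore course.

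**What to change.** 1. Record a course identifier for every intervention patient as the courses run.
2. Analyse the primary outcome with a random effect for course in the intervention arm only, each control being its own cluster, and a small-sample degrees-of-freedom correction such as Satterthwaite. If the logistic form is kept, it needs the course term too.
3. State the planned number and size of courses and an assumed ICC, with a range.
4. Restate power for 43 per arm on that basis.

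The cost is one database variable, some SAP wording, wider intervals, and a restated power that may be clearly below 95% if courses are few and large. A variance component from 2 to 4 courses will also be poorly estimated, and the report should say so. No extra patients are required. Running more, smaller courses where feasible would limit the loss.

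For scale, holding 95% by numbers alone, before any degrees-of-freedom correction, would take about 52 per arm at m = 10, ICC 0.05 (32.9 × 2.45 / 2 = 40.3, so 41; 41 / 0.8 = 51.3). At m = 15, ICC 0.10 it would take 70 (32.9 × 3.40 / 2 = 55.9, so 56; 56 / 0.8 = 70).

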**Figure 2. F2:**
[figure not shown]
Intervention design: 12 h of healthy habits education (nutrition, chronobiology, and physical exercise) distributed over 2 wk into 3-h sessions 2 d per wk.

### 2.2. Study population

The study subjects of both the quantitative and qualitative phases will be people diagnosed with FM, with or without CFS treated by public primary care centers of the Catalan Health Institute (ICS) in the region Terres de l’Ebre (Catalonia). The International Classification of Diseases-10 was applied^[34]^: M79.7 (FM) and G93.3 (CFS; myalgic encephalomyelitis).

*Study population and inclusion criteria*: People aged 18 to 65 with a recent diagnosis (<10 years) of FM, or a recent diagnosis of FM and CFS, with availability and interest in participating.

*Exclusion criteria*: Not meeting the inclusion criteria, participating in other ICS group interventions aimed at the treatment of these syndromes, presence of severe mental, comorbidity or other relevant medical disorders or pathologies that may interfere with the development of the intervention.

## 3. Quantitative study

### 3.1. Study variables

Main dependent variable: The main variable to be evaluated will be quality of life, assessed with the EuroQol-5D questionnaire.^[35]^

Secondary dependent variables: Fatigue will be assessed with the multidimensional fatigue inventory,^[36]^ consisting of 20 items and several dimensions. Sleep quality and insomnia will be evaluated with the Pittsburgh Sleep Quality Index-19 items.^[37]^ The VAS questionnaire will be used^[38]^ to assess pain. Adherence to the Mediterranean diet will be evaluated with the 17-item erMEDAS questionnaire.^[39]^ Physical exercise and sedentary lifestyle will be assessed with the REGICOR short questionnaire.^[40]^ In addition, circadian biological rhythm will be assessed with the biological rhythms interview of assessment in neuropsychiatry questionnaire,^[41]^ and anxiety with the Hospital Anxiety and Depression Scale.^[42]^ Moreover, people diagnosed with FM will be assessed with the FIQ-R.^[43]^ Food intake will also be evaluated using 24-hour reminders and a FFQ.^[44]^ Body composition will be analyzed through bioimpedance, strength and endurance using various validated tests, such as the 6-min walk test, the 30 second sit to stand test and hand dynamometer measurements.^[45]^

Independent variables: Sociodemographic variables (sex, age, educational level, profession, employment situation, size of city of residence, and comorbidity).

### 3.2. Data collection

Sample size and sampling procedure: The sample size was calculated by GRAMNO V7.12. sample size calculation program and is based on the variations we expect to observe in the EuroQol-5D questionnaire on health-related quality of life.^[35]^ Accepting an alpha risk of 0.05 and a beta risk of <0.05 in a 2-tailed test, a minimum of 43 subjects are needed in each group to detect a minimum difference of 1.6 between 2 groups, with a standard deviation of 1.8. The loss to follow-up rate was estimated at 20%.

Patients diagnosed with FM (ICD-10 code M79.7) with or without CFS (Myalgic encephalomyelitis, code G93.3) treated at Terres de l’Ebre ICS Primary Care (Catalonia) and who meet inclusion criteria will be contacted by phone and invited to participate in the study. Patients will be asked to come to the health center for the first visit, where the study will be explained, and informed consent signatures will be collected. A randomization list will be generated following Efron procedure^[46]^ and using the statistics program SPSS. At this visit, the patient will be informed of which group they will participate in (control or intervention) and the schedule of sessions (or visits). Additionally, the baseline data will be collected from self-administered questionnaires (EuroQol-5D, multidimensional fatigue inventory, VAS pain, Pittsburgh Sleep Quality Index, erMEDAS-17, biological rhythms interview of assessment in neuropsychiatry, REGICOR-Short, FIQR, Hospital Anxiety and Depression Scale) using Microsoft Forms or paper if participants have difficulty using technology. These data will be collected again at 1, 3, 6, and 12 months post-intervention (Table 1). Data will also be collected in person at baseline and at 3 and 6 months post-intervention to evaluate the food intake, body composition, strength and endurance of study participants. These data will be collected from both the intervention and control groups and will be entered into an Excel database for use in the various analyses.

**Table 1 T1:** Data collection planning.

Data collection	Baseline	1m post	3m post	6m post	12m post
To assess quality of life and symptoms, chronobiology and healthy habits (ONLINE):					
*EuroQol-5D: quality of life*	X	X	X	X	X
*MFI (20-items): fatigue*	X	X	X	X	X
*VAS pain: visual analogue pain intensity scale*	X	X	X	X	X
*PSQI (19 items): sleep quality*	X	X	X	X	X
*BRIAN: biological rhythm*	X	X	X	X	X
*REGICOR-Short: practice of physical exercise and sedentarism*	X	X	X	X	X
*Er-MEDAS-17: adherence to Mediterranean diet*	X	X	X	X	X
*FIQ-R: functional impact of fibromyalgia*	X	X	X	X	X
*HADS: anxiety and depression*	X	X	X	X	X
To assess endurance, strength and body composition (in person):					
*Anthropometry* and body composition via bioimpedance and waist circumference	X		X	X	X
Resistance via 6-min walk test	X		X	X	X
Upper trunk strength via dynamometer/handgrip measure	X		X	X	X
Lower trunk strength via 30 s sit to stand test	X		X	X	X
To assess chrononutrition, energy intake and macro- and micronutrient intake (in person):					
24-h reminder	X		X	X	X
FFQ Short	X		X	X	X

BRIAN = biological rhythms interview of assessment in neuropsychiatry, FFQ = food frequency questionnaire, FIQ-R = revised fibromyalgia impact questionnaire, HADS = Hospital Anxiety and Depression Scale, MFI = multidimensional fatigue inventory, PSQI = Pittsburgh Sleep Quality Index.

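### In the written order of the first visit, patients learn their group before they complete the self-reported baseline questionnaires, and nothing in the text puts the baseline first

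*Protocol article*

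**What the plan says.** Section 3.2 describes the first visit. The study is explained and consent is signed. The text then says "A randomization list will be generated following Efron procedure". Two statements follow, one directly after the other:

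- "At this visit, the patient will be informed of which group they will participate in (control or intervention", together with the schedule of sessions or visits.
- "Additionally, the baseline data will be collected from self-administered questionnaires", with the EuroQol-5D first in the list, to be completed "using Microsoft Forms or paper if participants have difficulty using technology".

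Section 2.1 describes the study as a "nonblinded, pragmatic randomized clinical trial with parallel groups". Section 3.1 fixes the primary outcome: "The main variable to be evaluated will be quality of life, assessed with the EuroQol-5D questionnaire". The only other statement on when the baseline is taken is in Section 2.1, in the description of the intervention, where data are to be collected "before intervention and during follow-up at 1, 3, and 6 months after intervention".

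Section 3.3 uses the baseline directly: "in the same group before and after intervention, the effect size will be calculated using Cohen d". It then names logistic regression for improved quality of life and does not say how improvement is determined.

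**The concern.** Randomisation makes the arms comparable at baseline only if the baseline is measured without knowledge of the group. Once patients know it, a self-reported baseline becomes in part a response to the allocation. The contrast between arms is easy for a patient to see: controls get usual practice (an individual visit and a leaflet), and the intervention group also gets 12 hours of group sessions. Hope or disappointment could move ratings of quality of life, fatigue, pain, sleep or anxiety by different amounts in the two arms.

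The baseline is one half of every before/after contrast, so such a shift passes into that contrast. It cannot be repaired later, because no uninfluenced baseline would exist for those patients.

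**Working it through.** **1. Order of events.** Section 3.2 states outright that the group is disclosed at the first visit. The questionnaires come in the next sentence, joined by a word that adds an item without fixing a sequence. Section 2.1 requires only that data precede the intervention, and a baseline taken after disclosure but before the first session meets that requirement. Nothing in the text puts the baseline before disclosure. Staff who follow the written order would collect it afterwards.

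**2. The plan's own figure.** Inputs from Section 3.2: difference 1.6, SD 1.8, two-sided alpha 0.05, beta below 0.05 (taken as power 0.95), loss to follow-up 20%.

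- n per group = 2 × [1.8 × (1.960 + 1.645) / 1.6]² = 32.9, rounded up to 33.
- Adding one for the t distribution gives 34, and 34 / 0.8 = 42.5, rounded up to the stated 43. Without the extra one, 33 / 0.8 = 41.25, rounded up to 42.

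The stated 43 is therefore reproduced if it already includes the loss allowance, and the present point does not change it. About 43 × 0.8 = 34 per group would be analysed. The planned effect is 1.6 / 1.8 = 0.89 SD.

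**3. What a shifted baseline would do.** The documents give no size for the shift. Let s be the difference between arms in the baseline shift, in SD units, with assumed values 0.1 to 0.3. Let r be the baseline-to-follow-up correlation, assumed 0.3 to 0.7. Follow-up scores, SD and r are taken as unchanged.

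- Before/after d within an arm (named in the plan): if the shift falls in one arm and d is scaled by the cross-sectional SD, that arm's d moves by s, that is by 0.1 to 0.3. The small and moderate bands in Section 3.3 are each 0.3 wide (0.2 to 0.5 and 0.5 to 0.8).
- Between-arm change score (not named in the plan, illustration only): bias = s × 1.8.
- Baseline-adjusted comparison (also illustration only): bias = r × s × 1.8.
- Comparison of follow-up scores alone: bias from this source = 0.

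| s (SD) | Change-score bias (points) | Share of 1.6 | Adjusted bias at r = 0.5 (points) |
|---|---|---|---|
| 0.1 | 0.18 | 11% | 0.09 |
| 0.2 | 0.36 | 23% | 0.18 |
| 0.3 | 0.54 | 34% | 0.27 |

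**4. False-positive rate with no true effect, 34 per group.** For the change score, SE = √[2(1 − r)] × √(2/34) in SD units. For the adjusted analysis, SE = √(1 − r²) × √(2/34). At r = 0.5 these are 0.243 and 0.210. The two-sided rate is the probability that a normal variable with mean bias/SE lies beyond ±1.96.

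| s (SD) | Change score, r = 0.5 | Adjusted, r = 0.5 |
|---|---|---|
| 0.1 | 7% | 6% |
| 0.2 | 13% | 8% |
| 0.3 | 24% | 11% |

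Over r = 0.3 to 0.7 the change-score rate runs from 6% to 36%, and the adjusted rate from 5% to 23%. If the bias ran against the intervention, a true change-score difference of 1.6 would appear as 1.42 to 1.06 points (1.6 − 0.18 to 1.6 − 0.54).

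**The case against.** The strongest reply is that the order is inferred. The linking word does not set a sequence, and the paragraph is not strictly chronological: it mentions the in-person baseline measurements only after the 12-month questionnaire follow-up. Figure 1, the flow diagram, is not available and may show the baseline before allocation. A condensed article may also leave the steps of a visit to the full protocol. This stands as a limit on certainty. A reader might infer that the baseline will certainly be taken with the group known; the text does not establish that. But the article does describe the visit, and the order it gives is the one that carries the risk.

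Other parts of the reply also stand:

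- **Analyses.** Section 3.3 names neither a change-score test between arms nor adjustment for baseline score, so those figures illustrate scale and do not describe the planned analysis. It would be wrong to say that every analysis is affected.
- **In-person tests.** A reader might infer that these too are done with the group known. Section 3.2 says only that they take place at baseline, without giving the visit or the timing relative to disclosure.
- **Early withdrawal.** One might argue that disappointed controls would leave without a baseline. If disclosure and questionnaires share a visit, this needs a patient to leave midway, and nothing in the article suggests it.
- **Nonblinded follow-up.** Follow-up answers are given with the group known in any case. That is inherent in this design, whereas the effect on the baseline can be avoided.

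**Conclusion.** The point holds as a weakness in how the first visit is written. Disclosure at that visit is explicit, the self-reported baseline (including the primary outcome) follows it in the text, and nothing shown reverses the order. Knowledge of the group may then bias the before/after Cohen d, and also the improvement outcome if improvement is defined from baseline. Random allocation itself is intact, and a comparison of follow-up scores alone does not carry this bias.

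Whether any shift would occur, how large, and in which direction are unknown. The range of 0.18 to 0.54 points (about 11% to 34% of the planned 1.6) rests entirely on assumed shifts of 0.1 to 0.3 SD. Baseline adjustment would shrink the bias to about r times that without removing it. The documents do not support the stronger statement that the baseline is already compromised. The case for acting is that the loss could not be repaired after enrolment and prevention costs very little.

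**What to change.** State the order of the first visit in Section 3.2 and follow it:

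1. Obtain consent.
2. Have all baseline questionnaires, online or on paper, completed and submitted.
3. Only then reveal the allocation and the schedule of sessions or visits.

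Where the in-person baseline tests take place at the same visit, do them before step 3 as well. If staff already work in this order, one sentence saying so settles the matter.

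This changes neither the sample size, the intervention nor the data items. The small cost is that patients must finish the questionnaires at the visit before they learn their group, so they cannot complete them later at home. Who holds and releases the randomization list is a separate question of allocation concealment, and this change does not depend on it.
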